## Abstract

**Background:**

Primary care is the initial contact point for most patients with opioid use disorder (OUD) but lacks tools for guiding treatment. Only a small fraction of patients access evidence-based care. Long-acting injectable buprenorphine has potential to improve medication adherence and program retention in low-barrier primary care treatment settings. We present the first clinical decision support algorithm incorporating long-acting buprenorphine (LAIB) in primary care. We include a protocol for a future evaluation of the algorithm’s implementation process, “Medication for Opioid Use Disorder (MOUD) 2.0,” at a housing and integrated care clinic at a Federally Qualified Health Center.

**Methods:**

Literature review and expert consensus informed creation of the algorithm, which underwent iterative development with feedback from clinicians, staff, and patients. Patients are categorized by adherence to therapy and retention in the program, with recommendations for each category. Adherence is determined by urine screen supplemented by self-report. To ensure all patients in this high morbidity and mortality risk population are treated, we will treat patients as their own controls in the evaluation, with potential for multisite comparisons. We will present descriptive statistics for adherence proportion before and after MOUD 2.0 implementation, testing for differences using McNemar’s test. We will then present pre- and post-implementation unadjusted six-month survival curves for retention.

**Discussion:**

LAIB is incorporated as an alternative or adjunctive treatment for patients refractory to sublingual buprenorphine and as an initial treatment for selected patients. We developed an algorithm with 4-, 8-, and 12-week decision points to guide treatment for patients with varying levels of response to sublingual buprenorphine and LAIB. This clinical decision tool incorporates LAIB among treatment options for OUD in primary care settings. The protocol will evaluate the algorithm’s implementation, presenting a replicable method for assessing adherence and retention among high-risk patients in similar settings.

## Background and rationale

The opioid epidemic accounts for high morbidity and mortality in the United States, contributing to 68,630 deaths in 2021 and 81,806 in 2022 (1–3). Social isolation (4) and declines in institutions of meaning and connection—e.g., family, religious communities, local and voluntary associations—contribute to increasing prevalence of opioid use disorder (OUD) and complications, leading to drops in life expectancy (5). Primary care is the first line of treatment for OUD in most communities. Yet, fewer than 25% of patients with OUD who interact with primary care receive highly effective medication for opioid use disorder (MOUD) (6). As many as 26-60% of motivated patients depending on population may fail to gain access to timely treatment with a clinician (7, 8). To address social and medical factors of this multifaceted epidemic, primary care needs clinical support tools and screens for an integrative approach.

Against increased mortality and availability of high-potency opioids, new treatment options such as long-acting injectable buprenorphine (LAIB) have emerged (9). Buprenorphine is a partial opioid agonist effective in preventing relapse, controlling withdrawal symptoms, and reducing overdose risk (10). Prescribed as a sublingual film or tablet, buprenorphine has seen increasing use in the primary care setting through practitioner education programs (11, 12). Buprenorphine has a long elimination half-life of 24-48 hours and reaches maximum serum concentration within 2 hours when taken sublingually, compared to around 12 hours to maximum concentration for LAIB [see (13)].

Yet, clinicians have recognized limitations to sublingual buprenorphine such as difficulty with adherence and diversion to non-clinical uses. Measuring adherence to buprenorphine relies on questionnaires alongside urine samples or buccal swabs, often generating equivocal results (14). In contrast to sublingual buprenorphine, as a new injectable route, LAIB can improve adherence while mitigating social factors associated with misuse and diversion (15). Among patients starting with fentanyl-positive urine in one randomized clinical trial, LAIB was associated with a significantly higher percentage of subsequent fentanyl-negative urine samples, compared to sublingual buprenorphine-naloxone (difference, 12.7%; 95% CI, 9.6%-15.9%) (16). Currently, injectable buprenorphine is much more expensive than sublingual buprenorphine. Judicious prescription thus balances potential benefits with costs to patients and clinics.

There are currently no guidelines for incorporating LAIB into stepwise treatment of OUD, so no algorithms and implementation studies yet exist. A PubMed search of the terms “MOUD, MAT, algorithm” in December 2023 yielded few results. Still, one description of a clinical algorithm (17) served as a good starting point for developing this study, in combination with the Substance Abuse and Mental Health Services Administration recommendations (18) and the American Society for Addiction Medicine practice guidelines (19). The previously proposed algorithm did not use results of drug testing, i.e. toxicology, to guide clinical decisions. Further, no studies to date included LAIB for clinical decision-making.

Filling these OUD treatment gaps and building on the aforementioned studies, treatment of OUD should ideally be fair, adaptable to patient response, and feasible within clinics’ resource limitations. To be perceived as fair, treatment must be consistent. Clinicians should consider objectively measurable and subjectively reported patient responses to treatment within a systematic framework, i.e., measurement based care (20, 21). We therefore developed a clinical decision support algorithm for treating OUD using measurement-based care in a primary care setting. This implementation study will evaluate the algorithm’s effects in an integrated primary and behavioral health setting. The following includes the implementation evaluation protocol followed by a full description of the algorithm.

## Methods

### Study objectives

The objective of this implementation evaluation is to assess whether the MOUD 2.0 algorithm improves treatment adherence and retention in the treatment program at the clinic-wide level, compared to these outcomes before implementation. The primary outcome measures are quantified adherence to MOUD and time length of retention in the treatment program.

Adherence will be operationalized as having a minimum of 3 buprenorphine appropriate drug screens (resulting positive for buprenorphine and norbuprenorphine) over a 6-month period regardless of substance use. Retention in treatment will be measured as the proportion of participants with at least 180 days of continuous pharmacotherapy with a medication prescribed for OUD, with no gaps greater than seven days (22). These outcome measures will show whether retention rates increase along with adherence, or whether the implementation favors one outcome measure over the other. The two measures are not mutually exclusive. In the context of an implementation evaluation, adherence could theoretically be more indicative of clinical response to the algorithm, whereas retention could characterize patient buy-in of the implementation. Secondary outcomes will include the percentage of patients starting LAIB for the first time, illicit use of substances per self-report and toxicology, and results of infectious disease while in the program.

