### Evaluation procedures, data sources, and variable abstraction

Evaluation procedures are limited to review of medical records that will already be in existence. The evaluation will include participants who received treatment for OUD between 6/1/2022 and 1/1/2024 and a random sample of patients without OUD within the same date range. Follow up information will be included on all participants up until 1/1/2025.

Data will be collected through retrospective chart review of the ICC’s electronic medical record. Corresponding to the listed date ranges, these data will be measured at six months before implementation of MOUD 2.0 and six months after implementation. Data will then be de-identified and sent to team members for analysis.

Demographics and medical history will have already been included in the electronic medical record from the standard intake forms used to begin patient encounters. Variables to be abstracted from the medical record include:

Demographic information: age, sex, racial self-identification.Adherence to MOUD (categorical, based on positive buprenorphine toxicology or concurrent negative opioid and buprenorphine toxicology) at collection time point.Use of opioids during treatment periods.Months in MOUD program, up to 1 year.Month/year of MOUD visits.Month/year of LAIB injection.Results of urine drug screens while in program.Treatment Effectiveness Assessment Score (21).Results of HIV/HCV screening labs while in program.Dates, dosage, and quantity of buprenorphine prescriptions.

Adherence is difficult to determine from self-report in patients with OUD due to factors like diversion, stigma, and bias (26, 27). Previously published non-LAIB algorithms did not incorporate objective measures besides self-report. To improve accuracy in treatment, adherence will be determined based on toxicology as described in the algorithm.

The approach to urine drug screening was non-standard in the months prior to implementation and continues to reflect the harm reduction approach to treatment. Therefore, adherence will be operationalized as having a minimum of 3 buprenorphine- and norbuprenorphine-positive (“appropriate”) drug screens over a 6-month period regardless of substance use. Each screen should be at least 2 weeks apart within this time period. In each phase of the evaluation, participants will be dichotomized into “adherent” vs “non-adherent” using the above definition.

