### MOUD 2.0 algorithm

The MOUD 2.0 algorithm was implemented at the clinic-wide level in January 2023. Staff at the ICC, Pathways to Housing PA, and PHHS developed the algorithm for use at follow-up visits for OUD after the initial diagnosis visit (see **Table 1** and below **Figure 1**). The algorithm has 4-, 8-, and 12-week decision points to guide treatment for patients with varying responses to sublingual and injectable buprenorphine.

**Table 1 T1:** MOUD 2.0 status and algorithm responses.

Status	Symptoms	Opioid Use	Opioid level	BUP adherence	BUP level	Plan	Visit interval
Full response	Improved	None	Negative	Full	Appropriate	Continue current dose	2 weeks in-person alt 2 week TH option OR 4 weeks in-person
Partial response with BUP	Improved	Some	Positive	Partial	Appropriate	Consider: Increase dose Regular BH f/u LAIB	2 weeks in-person alt 2 week TH option
Partial response without BUP	Improved	Some	Positive	Partial	Negative OR Adulterated OR Late	Review dosing method Consider: Increase dose Regular BH f/u LAIB	2 weeks in-person for up to 12 weeks LAIB or refer at week 12
Minimal or nonresponse without BUP	No improvement	Some	Positive	Partial	Negative OR Adulterated OR Late	Review dosing method Consider: Increase dose Regular BH f/u LAIB	2 weeks in-person for up to 8 weeks LAIB or refer at week 8
Reconsider diagnosis of OUD	Any	Any	Negative	Any	Negative OR Adulterated OR Late	Review hx/reconsider diagnosis of OUD	2 weeks in person Discharge or refer at 4 weeks

“Appropriate” indicates buprenorphine and norbuprenorphine detected in urine without contaminants.

*BUP* buprenorphine, *BH f/u* behavioral health follow up, *LAIB* long-acting injectable buprenorphine, *OUD* opioid use disorder, *alt TH* alternating telehealth.

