**Figure 1 f1:**
[figure not shown]
Clinical decision algorithm for treating opioid use disorder with sublingual and injectable buprenorphine.

Patients are clinically categorized as “full response,” “partial response with buprenorphine,” “partial response without buprenorphine,” “minimal or nonresponsive without buprenorphine,” and “reconsider diagnosis of OUD.” Note that “full” or “partial response” in the algorithm refers not to adherence or non-adherent outcomes but are clinical categories of physiological response informing further treatment decisions. Physiological response is important *within* the algorithm but is not an outcome measure for successful algorithm implementation.

Depending on the response, the algorithm recommends a plan and follow-up interval. Categories are based on subjective improvement of OUD symptoms in response to buprenorphine, in combination with objective measures of MOUD adherence. Symptoms include cravings, withdrawals, and interference with other activities and functioning with reference to DSM-5 diagnostic criteria for OUD, and are subjectively reported by the patient as improved, the same, or worse compared to the previous visit.

Because a major goal of MOUD 2.0 is increasing buprenorphine adherence, toxicology is included as a clinical data point to guide decision-making (28). Patients subjectively report non-prescribed opioid use, which is confirmed by urine or saliva drug screen including fentanyl and other opioids. Urine testing for appropriate levels of buprenorphine and metabolites confirms buprenorphine adherence. The combination of subjective patient report, urine opioid screen, and urine buprenorphine testing results in the patient’s status that the algorithm assigns (see **Table 1**).

For example, “full response” patients report improved symptoms, demonstrate appropriate qualitative levels of buprenorphine and its metabolite norbuprenorphine, and show no evidence of opioid use on urine screen. Improved symptoms include findings such as fewer cravings, better functioning in everyday activities, and less time spent for obtaining opioids, etc. (19). These patients continue their regimen of buprenorphine and clinic visits every 2-4 weeks, at shared discretion. Buprenorphine dose will remain unchanged as their current dose and delivery route of buprenorphine appear to be working well.

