### Algorithm development, staffing, and funding in a low-barrier setting

The ICC, the setting for the development of the algorithm, provides medical, behavioral health, substance use treatment, and housing services. Since 2016, the clinic’s services have included low-barrier, primary care-based MOUD. The low-barrier approach was first described with methadone maintenance therapy (29) and has been extended to buprenorphine treatment (30). This approach includes same-day treatment entry, harm reduction, flexibility in appointments and prescribing, and combining services in one location.

The ICC participates in the Pathways housing-first model, which offers immediate access to one-bedroom scattered-site apartments with intensive support services for people with experiences of chronic homelessness. All participants have a diagnosis of a serious mental illness or substance use disorder. Many participants were previously living unsheltered in the Kensington neighborhood of Philadelphia, a neighborhood often called the “epicenter of the opioid crisis,” with high levels of OUD, homelessness, food insecurity, and early mortality (31–33). The ICC continued increasing the number of people treated for OUD and modified its services throughout the COVID pandemic. As multiple other low-barrier MOUD clinics have reported, the ICC MOUD program made several intentional adjustments to MOUD care delivery to facilitate access despite disruptions. Such adjustments included: 1. extended visit intervals of up to 2 weeks during the initiation and stabilization phase of treatment with telehealth options, and, 2. a goal of monthly urine drug screening for all patients, but tolerating longer intervals without penalty.

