### Data analysis

Baseline and demographic characteristics will be summarized with descriptive statistics such as means and standard deviations for continuous variables such as age and percentages for categorical variables such as race.

To accommodate the need for OUD treatment centers to have fair and ethical treatment of patients at the clinic-wide level, we will use patients as their own controls and assess six-month adherence before and after program implementation. The evaluation will follow the same patients, either adherent or non-adherent at six months before algorithm implementation, by chart review to see if they crossed over to the opposite outcome six months after implementation. We will present adherence at endpoints six months prior to and six months after MOUD 2.0 implementation as proportions. We will qualitatively compare the proportion of adherence six months prior, i.e. adherence in 2022, to the proportion six months after. Then, a chi-squared test will compare discordant pairs, i.e. patients who became newly adherent after MOUD 2.0 and patients who became newly non-adherent.

Because we are treating adherence as a binary outcome, we will use McNemar’s test to determine differences in adherence before and after implementation, with each individual patient before and after implementation as a paired sample. The Chi-squared test statistic for McNemar’s test takes the form:

$$\chi^{2}=\frac{{\left(b-c\right)}^{2}}{b+c}$$

where χ^2^ follows the chi-squared distribution with 1 degree of freedom, *b* represents the patients who were adherent before and were not adherent after, and *c* represents the patients who were not adherent before and were adherent after.

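### Adherence counts appropriate screens without regard to how many were taken, so the before/after McNemar test can move with screening frequency alone

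*Protocol article*

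**What the plan says.** The outcome is defined in the protocol article under Study objectives: "Adherence will be operationalized as having a minimum of 3 buprenorphine appropriate drug screens (resulting positive for buprenorphine and norbuprenorphine) over a 6-month period". The section on evaluation procedures and data sources repeats it and adds one condition, "Each screen should be at least 2 weeks apart within this time period". In each period, "participants will be dichotomized into “adherent” vs “non-adherent” using the above definition".

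That section introduces the rule as the response to uneven testing: "The approach to urine drug screening was non-standard in the months prior to implementation and continues to reflect the harm reduction approach to treatment". The section on algorithm development describes the clinic's practice as adjusted during the pandemic: "a goal of monthly urine drug screening for all patients, but tolerating longer intervals without penalty".

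After implementation, the MOUD 2.0 algorithm section says "toxicology is included as a clinical data point to guide decision-making". Table 1 sets the visit interval by response status; for full responders it is "2 weeks in-person alt 2 week TH option OR 4 weeks in-person". Partial responders without buprenorphine in urine and non-responders are seen in person every 2 weeks for up to 12 and 8 weeks respectively.

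Under Data analysis, "a chi-squared test will compare discordant pairs, i.e. patients who became newly adherent after MOUD 2.0 and patients who became newly non-adherent", by McNemar's statistic without continuity correction, among patients enrolled before implementation.

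**The concern.** A count of positives with no denominator mixes two things: whether the patient takes buprenorphine, and how often anyone checked. Fewer than 3 spaced screens makes a patient non-adherent whatever the results show. The 2-week spacing stops clustered screens from counting more than once, but it does not give a patient the same number of chances in both periods. A fixed count therefore does not solve the problem of uneven screening that it was chosen to address.

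Using patients as their own controls does not help, because the number of screens can change within the same patient. The algorithm also includes the measurement from which the outcome is built. Adherence is a primary outcome, and McNemar's is the only test the article specifies for a primary outcome. A significant result could mean that more patients take their medication, or that the same patients are screened more often. A fall in screening would push the result the other way.

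**Working it through.** **Inputs from the article.** At least 3 appropriate screens in 6 months, 2 weeks apart; McNemar statistic (b − c)²/(b + c) on 1 degree of freedom, where b is adherent then not and c is the reverse; about 100 participants in all. A monthly goal, or one in-person visit every 4 weeks, gives about six screens in 6 months. The article has no figure of its own to reproduce here: it gives no screen counts and no expected adherence, and its sample size of 86 comes from a proportional-hazards formula that does not enter this point.

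**Assumptions.** Screens per patient n; chance p that a screen is appropriate, the same in both periods and independent between screens; two-sided 5% level; 50 or 100 pairs. The paired cohort is only part of the roughly 100 participants, so 100 is an upper case.

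**Step 1: chance of being scored adherent.** P = Σ C(n,k) pᵏ(1−p)ⁿ⁻ᵏ over k = 3 to n. At p = 50%, four screens give (4 + 1)/16 = 31%; six give 1 − (1 + 6 + 15)/64 = 42/64 = 66%.

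| p | n=2 | n=3 | n=4 | n=5 | n=6 |
|---|---|---|---|---|---|
| 30% | 0% | 3% | 8% | 16% | 26% |
| 50% | 0% | 13% | 31% | 50% | 66% |
| 80% | 0% | 51% | 82% | 94% | 98% |

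**Step 2: McNemar with medication taking unchanged.** Let a and d be a patient's probabilities of being scored adherent before and after, with the same p. The discordant probabilities are P(b) = E[a(1−d)] and P(c) = E[(1−a)d]. With p uniform on 0 to 1, E[a] = (n−2)/(n+1): 2/5 = 40.0% for four screens and 4/7 = 57.1% for six. Four then six screens gives P(b) = 0.0442 and P(c) = 0.2156. With 100 pairs the expected counts are 4.42 and 21.56, and (21.56 − 4.42)²/25.98 = 11.3, against a critical value of 3.841.

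Exact multinomial summation over b and c gives the chance of a significant result:

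| Screens before, then after (p uniform) | 50 pairs | 100 pairs |
|---|---|---|
| 6 then 6 | 4% | 5% |
| 5 then 6 | 17% | 35% |
| 4 then 6 | 69% | 95% |
| 20% of patients 2 then 6, the rest 6 then 6 | 33% | 61% |
| 10% of patients 2 then 6, the rest 6 then 6 | 12% | 22% |

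The first row shows that the test itself is sound when screening is equal.

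**Step 3: the same with one fixed p for all.**

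| Scenario | Pairs | p=30% | p=50% | p=80% |
|---|---|---|---|---|
| 4 then 6 | 50 | 63% | 94% | 84% |
| 4 then 6 | 100 | 92% | over 99% | 99% |
| 20% of patients 2 then 6 | 50 | 9% | 27% | 92% |
| 20% of patients 2 then 6 | 100 | 14% | 47% | over 99% |

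**Step 4: patients who mostly take or mostly do not take the drug.** With p distributed as Beta(0.2, 0.2), four then six gives 30% and 55% (50 and 100 pairs), and five then six gives 8% and 14%. The case where 20% of patients go from two to six rises to 46% and 78%.

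**The case against.** The strongest reply is that a rise in screening is inferred, not documented. The article says harm-reduction screening continues. The monthly goal belongs to pandemic-era practice, an approach the article dates to March 2020 to March 2022, so it is weak evidence for the six months before January 2023. Table 1 leaves many patients on in-person contact about every 4 weeks, or six screens, which equals the earlier goal; six then six gives no inflation. The fixed 2-weekly rows are time-limited and can end in referral or discharge, which cuts later screens. This stands: the size and direction of any shift are unknown, and the rejection rates are not expected error rates.

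The rates also depend on the spread of p, as Step 4 shows. They assume that the number of screens is unrelated to medication taking, whereas a patient with few screens may have lapsed, so that non-adherent is partly the right label. This stands too, and is a reason to show the groups separately.

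A third reply is that the authors chose a low threshold knowing screening was uneven. A low threshold softens the dependence when p is high (94% and 98% for five and six screens at p = 80%) but does not remove it. The limitations discussed in the article cover binary categories and general confounding, not unequal opportunity to be scored adherent.

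Finally, this might be left to an analysis plan. But the article itself fixes the definition, the dichotomy and the test, and the fault lies in those.

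**Conclusion.** The concern holds. As fixed, the adherence outcome can change between periods because of screening frequency alone, and the McNemar comparison cannot tell that from a change in medication taking. Under the assumptions shown, one fewer spaced screen per patient before implementation gives a 17% to 35% chance of a significant result with uniform p (8% to 14% with the polarised spread), and two fewer gives 69% to 95% (30% to 55%). Under-screening confined to a fifth of patients gives anything from 9% to over 99%, depending on p and cohort size. If patients had about the same number of screens in both periods, there is little or no problem. Screen counts, p, the 5% level and the size of the paired cohort are all assumptions. The mechanism is certain; its size in this clinic is not. It should be dealt with before the results are read.

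**What to change.** Keep the primary definition and McNemar's test. For the pre-enrolled cohort, in each period:

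- **Report** the number of eligible spaced screens per patient and how many were appropriate. The number taken alone is not enough, because patients with 3 or more screens still differ by frequency (13% with three and 66% with six at p = 50%).
- **Split** the non-adherent group beside the McNemar table: in the programme with 3 or more spaced screens but fewer than 3 appropriate; in the programme with fewer than 3 spaced screens; left the programme.
- **State in advance** that a McNemar difference will not be read as a change in medication taking if it is driven by the group with fewer than 3 spaced screens, or if screens per patient changed while the share appropriate did not. Fix beforehand what counts as driven and as changed. One option for the former is that more than half of the net shift c − b comes from pairs with fewer than 3 spaced screens in either period.

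Optionally, where the chart records it, show referral or discharge directed by the algorithm (Table 1, weeks 4, 8 and 12) apart from other dropout when describing patients not retained.

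The cost is a small descriptive table and a short interpretation rule. Urine screen results are already abstracted, and the spacing rule already requires screen dates; no new patients or procedures are needed. Cells will be small, and the share of appropriate screens can depend on who was chosen for testing, so the table should stay descriptive, with no test.

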Finally, we will present unadjusted six-month survival curves for retention before and after implementation. While comparing unadjusted survival curves before and after MOUD program implementation has potential for survival bias (i.e., individuals need to “survive” to program implementation in order to be considered for post-implementation calculations), this comparison is given to provide a general sense of how MOUD 2.0 might affect the clinic overall and not to predict explicit dropout rates. If there is a significant number of patients not retained, descriptive statistics for this group will be reported to characterize factors associated with dropout. Secondary outcomes such as receipt of LAIB and use of opioids and of other substances during the evaluation periods will be analyzed with linear regression models for descriptive purposes. These primary and secondary outcomes may also be used for a future stepped wedge analysis in other clinics that could use the algorithm prospectively.

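### Retention is a primary outcome defined two ways and analysed only by descriptive curves, so no pre/post effect is estimated; its 180-day proportion is also open to a follow-up artefact if late starters are counted

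*Protocol article*

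**What the plan says.** All references are to the protocol article.

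- **Study objectives.** The aim is to "assess whether the MOUD 2.0 algorithm improves treatment adherence and retention in the treatment program at the clinic-wide level", compared with before implementation. The primary outcomes are "quantified adherence to MOUD and time length of retention in the treatment program". Retention is then operationalised as the "proportion of participants with at least 180 days of continuous pharmacotherapy" with a medication prescribed for OUD, allowing no gap over seven days.
- **Setting and population.** The pre curve is drawn from all aggregated patients in MOUD programs six months before implementation, followed to implementation or dropout. The post curve covers 6 to 12 months after implementation, or to dropout.
- **Evaluation procedures.** The evaluation includes "participants who received treatment for OUD between 6/1/2022 and 1/1/2024". "Follow up information will be included on all participants up until 1/1/2025".
- **MOUD 2.0 algorithm.** "The MOUD 2.0 algorithm was implemented at the clinic-wide level in January 2023"; the day is not given.
- **Data analysis.** Adherence gets McNemar's test with its formula. Retention gets unadjusted six-month survival curves, with survival bias acknowledged and the purpose stated as "to provide a general sense of how MOUD 2.0 might affect the clinic overall and not to predict explicit dropout rates". Patients not retained may also be described.
- **Sample size and power.** A figure of 86 comes from the proportional-hazards regression formula. About 100 patients are expected.

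**The concern.** There are two linked problems.

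First, the stated analysis does not match the stated objective. Asking whether retention improves calls for an estimated change and its uncertainty. Two curves without a contrast leave the reader to judge by eye. It is also unclear which outcome the curves represent: a length of time, or the proportion reaching 180 days. The proportional-hazards model behind the sample size is not among the analyses described.

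Second, the raw proportion needs every patient in its denominator to have 180 days available. In the pre period that depends on who is counted. If patients who start shortly before implementation are counted, they are recorded as not retained simply because the period ended. Part of any apparent gain would then be a product of unequal follow-up, in one of only two primary outcomes.

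**Working it through.** **1. The plan's own figure.** The article gives no hazard ratio, alpha, power or event fraction, so 86 can be neither confirmed nor refuted. Freedman's formula, d = (z_α/2 + z_β)² × (1 + HR)² / (1 − HR)², returns it from quite different inputs (equal groups, two-sided 5%):
- 80% power, HR 0.40, half the patients with an event: 7.849 × (1.40/0.60)² = 42.7 events; 42.7/0.5 = 85.5, rounded up to 86.
- 90% power, HR 0.48, every patient with an event: 10.507 × (1.48/0.52)² = 85.1, rounded up to 86.

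What matters here is that the figure presupposes a hazard-ratio analysis, whereas Data analysis lists McNemar's test, unadjusted curves and, for secondary outcomes, linear regression.

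**2. Who can reach 180 days before implementation.** The inclusion window opens on 6/1/2022. The implementation day is unknown, so three dates are tried. The share assumes new starts spread evenly over the window and equals (days − 180)/days.

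| Implementation | Days from 6/1/2022 | Last start allowing 180 days | Share of even new starters able to reach 180 |
|---|---|---|---|
| 1 January 2023 | 214 | 5 July 2022 | 34/214 = 16% |
| 15 January 2023 | 228 | 19 July 2022 | 48/228 = 21% |
| 31 January 2023 | 244 | 4 August 2022 | 64/244 = 26% |

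These shares apply to new starters only. A patient already in treatment on 1 July 2022 has 184 days to 1 January 2023 and can reach 180, with four days to spare.

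**3. Size of the artefact if all pre-period patients are in the denominator.** Let r be true 180-day retention, the same in both periods, and q the share already in treatment when the window opens. For implementation on 1 January:
- apparent pre proportion = r × [q + (1 − q) × 34/214]
- spurious gain = r × (1 − q) × (1 − 0.159)

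With r = 60% assumed:

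| q | Apparent pre | Spurious gain |
|---|---|---|
| 100% | 60.0% | 0 points |
| 80% | 49.9% | 10 points |
| 60% | 39.8% | 20 points |
| 40% | 29.7% | 30 points |

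Most of the pre-period group would be unable to reach 180 days only if q were below (0.5 − 0.159)/(1 − 0.159) = 41%.

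**4. Precision of an estimated difference.** With 1.96 × √[2p(1 − p)/n] and the periods treated as independent:
- n = 100 per period: 12.7 points at p = 70%, 13.9 at p = 50%
- n = 86 per period: 13.7 points at p = 70%, 14.9 at p = 50%

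**The case against.** The strongest defence is the cohort rule in Setting and population. Read naturally, the pre curve follows patients already in a program six months before implementation. They have about 184 days, so the artefact is nil. The clinic has provided MOUD since 2016 and its population is described as steady, so a low share of established patients is unlikely. Both curves span six months, so follow-up to 1/1/2025 is not the retention window, and the year or more available to post-period patients should not be set against the short pre period. A curve that ends at implementation or dropout can already be read near 180 days. Intervals are often left to a fuller plan, and the article openly limits what the curves are for.

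Most of this stands, and it rules out three stronger readings that a reader might infer:
- *That most pre-period patients cannot reach 180 days.* The 16% to 26% describes evenly spread new starters, whose share of the clinic is not given.
- *That the proportion must rise after implementation by construction.* It does so only if late starters are in the pre denominator.
- *That the retention question cannot be answered.* The data could support a 180-day estimate.

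The defence does not remove the core. The cohort wording also speaks of all aggregated patients, so both readings of the denominator remain open. And confining a primary outcome to a general impression is a declared purpose, not a detail lost in condensing; the same section gives the other primary outcome a named test.

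**Conclusion.** The concern holds in limited form. Retention is a primary outcome with two definitions, and its described analysis yields no pre/post effect estimate or interval. That does not fit an objective of showing improvement, nor a sample size taken from a hazard-ratio model.

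The follow-up artefact is conditional. It ranges from 0 points (all patients already in treatment) to about 30 points (40% already in treatment). This assumes 60% true retention, evenly spread new starts, implementation on 1 January 2023, and all pre-period patients in the denominator. The article does not give the share that would place the clinic on this scale. The point should be corrected before analysis, but it does not undermine the evaluation as a whole.

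**What to change.** 1. Define retention once, as the Kaplan-Meier probability of remaining on MOUD, with no gap over 7 days, for 180 days.
2. Use windows of equal length before and after implementation, each at least 180 days. Apply the same cohort rule to both, and state whether patients who start during a window are included.
3. Censor pre-period time at implementation, so that late starters contribute the time they have and are not counted as failures.
4. Take the window start as time zero for patients already in treatment. Use delayed entry from MOUD start only where start dates exist: the abstraction list records program time only up to one year and visits by month and year, so such dates are not assured for long-term patients.
5. Report the post-minus-pre difference with a 95% confidence interval from a bootstrap that resamples patients, because many are in both periods.
6. Do not report the raw 180-day proportion with late starters in its denominator.

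The cost is some wording and a short additional analysis; dated buprenorphine prescriptions are already on the abstraction list. The interval will be wide, roughly plus or minus 13 to 15 points at 50% to 70% retention with 86 to 100 patients per period treated as independent. Overlap between periods and censoring would change that width. The change does not remove the survival bias or the confounding that the article already acknowledges.
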